### Intervention

For the purpose of the current study, we selected as eligible treatment the VIPP-SD [14, 107], an evidence-based intervention aimed at enhancing parental sensitivity and sensitive discipline in parents of toddlers and preschool children. The protocol has proven to be effective in different randomized controlled trials in various populations [108–110], with a recent meta-analytic study reporting a combined effect size of *d* = 0.47 [21], and its characteristics appear particularly suitable for mothers with SUD.

Specifically, the limited number of sessions, the focus on interactive behaviors, and the home-based nature of the protocol are likely to help maintain the mothers’ engagement, limiting the risk of dropouts before the end of treatment [111–113]. The ease of understanding of the contents supports comprehension of the intervention themes, preventing dropout risks linked to deficits in attention and cognitive functioning [11, 13]. The use of the video-feedback technique, the focus on child signals [45], and the provision of information on child development could help mothers to adapt their interaction to the child’s age-appropriate level [114, 115]. These features support the feasibility of applying the intervention to this specific clinical population, offering the possibility to administer it both in the context of outpatient and inpatient conditions.

### Aims and hypotheses

Our primary aim is to investigate intervention effects on the quality of parenting measured through observed parenting behaviors, in mothers with SUD. We will investigate whether the intervention affects sensitive parenting and gentle but consistent discipline. We expect that, from pre-test to post-test, the quality of observed parenting in the SUD experimental group increases more or decreases less than in the SUD control group.Our secondary aim is to investigate intervention effects on parental cognitive mechanisms. We will investigate whether the intervention affects the mothers’ performances on (2a) an attentional bias reaction time paradigm aimed at measuring attentional bias to negative emotions and on (2b) a go/no-go task involving child faces displaying different emotions aimed at measuring inhibitory control in response to child emotions, respectively. Moreover, we will investigate whether the intervention affects (2c) self-perceived reflective functioning. We expect that the intervention modifies the mothers’ performances on the two tasks and self-reported reflective functioning in the SUD experimental group with respect to the SUD control group.Our tertiary aim is to investigate whether changes in parental cognitive mechanisms affect intervention effect on parenting. Specifically, we will investigate whether changes in the mothers’ (3a) attentional bias, (3b) inhibitory control, and (3c) reflective functioning account for changes observed in parenting. Specifically, we expect that improvements in the mothers’ performances on the cognitive measures will be associated to improvements in the quality of observed parenting in the SUD experimental group (Fig. 1).Our fourth objective is to explore whether the administration of the intervention has an effect on parenting stress. Specifically, we expect that, after the administration of the VIPP-SD, perceived parenting stress in the SUD experimental group decreases compared to the SUD control group.Our fifth objective is to compare the SUD experimental group and the SUD control group to the low-risk group with respect to post-test measures.

**Fig. 1 Fig1:**
[figure not shown]
Aims of the study and hypothesized mechanisms of change

## Methods/design

### Study design

The study is a randomized wait-list controlled trial aimed at investigating the role of parental inhibitory control, attentional disengagement, and reflective functioning in the efficacy of the VIPP-SD, an evidence-based parenting intervention, in mothers with SUD. The protocol was developed in line with the SPIRIT guidelines ([116], see Additional files 1 and 2). The project will involve a group of mothers with SUD and a group of low-risk mothers. The intervention will be randomly delivered to half of the mothers in the SUD group, through a wait-list approach. Specifically, mothers from the SUD group will be randomly assigned to one of two conditions: (1) an experimental condition (SUD experimental group), treated with the VIPP-SD, and (2) a wait-list condition (SUD control group), with TAU. Participants in both groups will be assessed pre- and post-treatment/wait-list for primary and secondary outcome measures. Participants in the SUD experimental group will be reassessed at a 2-month follow-up, to see whether outcomes measured during the post-test phase remain stable, whereas at the end of the post-test phase participants in the SUD control group will be administered the intervention.

Mothers in the low-risk group will undergo two measurements (respectively assessment 1 and assessment 2) where we will collect the same measures collected in the SUD group (quality of parenting behaviors, attentional disengagement, inhibitory control, reflective functioning, parenting stress, maternal general executive functioning, and psychopathology). The two measurements in the low-risk group are scheduled at a 3-month distance, a time frame that equals the length of the VIPP-SD, and will serve as a comparison for the pre-test and the post-test phase of the SUD experimental group. Figure 2 presents the diagram of participants’ flow through the trial.

**Fig. 2 Fig2:**
[figure not shown]
Diagram of participants’ flow through the trial

### Participants

#### Recruitment

The project will involve 60 mothers with toddlers and preschool children, aged between 12 months and 6 years old. The recruitment will be carried out in northern Italy. The SUD group (*n* = 40) will be composed of women with a history of SUD diagnosis recruited through residential and outpatient facilities that treat SUD and other psychiatric disturbances. History of SUD diagnosis is defined as severe substance use, abuse, or dependence, within 2 years preceding enrollment, with respect to one or more substances of interest (e.g., alcohol; caffeine; cannabis; hallucinogens; inhalants; opioids; sedatives, hypnotics, or anxiolytics; stimulants; tobacco; and other or unknown substances) according to criteria outlined by principal diagnostic manuals [2]. Studies on SUD identified a rate of dropout ranging from 23 to 50% in outpatient treatment [117, 118] and from 17 to 57% in inpatient treatment [119, 120]. In order to prevent attrition bias, and to reach the expected number of participants completing the trial, we will oversample participants in the SUD group by 20%. The low-risk group (*n*=20) includes mothers recruited from the general population. Mothers in the low-risk group should present the absence of history of SUD diagnosis and absence of history of treatment in residential and outpatient facilities that treat SUD and other psychiatric disturbances. We will screen them using a specific checklist administered at their enrollment. Inclusion criteria for each group foresee that mother and child live together or in close contact (at least 4 times per week) at the time of recruitment and during the various stages of the study. Exclusion criteria concern the presence of diagnosed psychotic disorders in an active phase, organic brain disorders that prevent the execution of the tasks, and child developmental pervasive disorders. Mothers in the SUD group will be contacted through the help of healthcare providers, whereas mothers in the low-risk group will be contacted through family centers, nursery schools, and academic database sources. Potential candidates will be invited to take part in the study and will receive more information and asked informed consent when they agree to participate. Participation in the study is free.

#### Randomization

Randomization of the SUD group to the SUD experimental and SUD control group will be carried out a priori and each participant will be assigned to a predetermined condition once enrolled in the study. We will adopt a blocked randomization with randomly selected block sizes, stratified with respect to child’s gender and age. Blocked randomization enhances the chance that treatment groups are equal in size and uniformly distributed according to key outcome-related characteristics [121]. Randomization will be implemented charging three distinct figures of sequence generation, participant enrollment, and participant allocation [122]. Sequence generation will be carried out by an independent researcher through R [123], with a 1:1 allocation using random block sizes of 2 and 4, stratified by gender and child age (younger vs older than 30 months). The researcher performing sequence generation will not be involved in recruitment, intervention administration, data collection, or data coding. To guarantee allocation concealment and to avoid selection bias, an independent researcher not involved in the trial will be charged to the custody of the sequences generated and to the assignment of the participants to each condition. Once the participants have been recruited and assessed for the pre-test phase, the researcher will be contacted by phone and hear the allocation of each individual.

#### Sample size and power

The sample size for the study was calculated based on power, level of significance, and size of the treatment effect expected [124], referring to previous study reporting on RCTs addressed to mothers with SUD [86]. Power was set at the conventional level of 80%. Regarding the size of the expected treatment, recent meta-analytic work testing the effectiveness of VIPP-SD on sensitive parenting yielded a combined effect size of *d* = 0.47, indicating that the intervention significantly increases sensitive caregiving [21, 125]. For the purposes of the present study, a statistical power analysis was performed for sample size estimation (repeated measures ANOVA within-between interaction, G*Power 3.1.9.2). For our primary, secondary, and fourth aims, testing the effect of the intervention on parenting and on parental cognitive mechanisms through repeated measures analyses with *α* = .05, a statistical power (1 − *β*) = 0.80, and a medium-sized effect of *d* = 0.47, a minimum sample size of *n* = 34 is required. For our third and fifth aims, testing mediating mechanisms, the proposed sample size ensures a power >80% since the power to detect mediating effects is generally larger than it is for main effects [126]. Considering the high risk of attrition in the SUD group, we will adopt oversampling strategies when managing missing data [127] and intention-to-treat analyses [128], in order to preserve statistical power.

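### The minimum of 34 mothers gives 80% power for a between-arm difference in change of about 0.94 to 1.0 SD, roughly twice the d = 0.47 cited; for 0.47 SD the power is well below 80% unless the pre-post correlation is about 0.87 or higher

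*Protocol article*

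**What the plan says.** All of this is in the Protocol article. Under Sample size and power, the effect comes from a meta-analysis: "recent meta-analytic work testing the effectiveness of VIPP-SD on sensitive parenting yielded a combined effect size of *d* = 0.47". The procedure is given as "repeated measures ANOVA within-between interaction, G*Power 3.1.9.2". For the primary, secondary and fourth aims, the section concludes that with α = .05, power of 0.80 and "a medium-sized effect of *d* = 0.47, a minimum sample size of *n* = 34 is required". Neither the effect size f entered in the program nor the pre-post correlation is reported. For the third and fifth aims the section claims power above 80% at the same sample size, on the ground that mediated effects are generally easier to detect than main effects.

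The randomised sample is given under Recruitment: "The SUD group (*n* = 40) will be composed of women with a history of SUD diagnosis". Under Randomization, the two arms are formed "with a 1:1 allocation using random block sizes of 2 and 4". Study design gives the two arms two assessments in common, before and after treatment or waiting. Statistical analyses plans a model with condition as the between-subjects factor and time as the within-subjects factor. Aims and hypotheses words the primary hypothesis as a difference between the arms in change.

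**The concern.** The procedure named takes Cohen's f for the interaction, not d. A standardised difference of 0.47 between arms has to be converted, and for a group-by-time interaction with two arms and two occasions the conversion is not d/2. If d/2, or the conventional medium f of 0.25, is entered, the program returns the sample size for a much larger effect than the one cited.

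At stake is the power statement for three of the five aims, and for the other two so far as they lean on it. A reader would take the trial to have an 80% chance of detecting the meta-analytic effect. If the real chance is far lower, a non-significant result says much less than that reader would suppose.

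**Working it through.** **Inputs.** From the article: two-arm 1:1 design, two common occasions, α = .05, target power 0.80, d = 0.47, stated N = 34, planned N = 40. Not stated: the pre-post correlation ρ and the f entered. I assume ρ = 0.5, which is the program's default and the value at which f = 0.25 returns 34, and then vary it.

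**Formula.** For k = 2 groups and m = 2 occasions, the interaction test has noncentrality λ = f²·N·m/(1 − ρ), with 1 and N − 2 degrees of freedom.

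**Step 1: reproduce 34.**
- f = 0.25, ρ = 0.5: λ = 0.0625 × 34 × 2/0.5 = 8.5. Power is 0.781 at N = 32 and 0.807 at N = 34, so the minimum is 34. This matches the article.
- f = d/2 = 0.235, ρ = 0.5: λ = 0.055225 × 34 × 2/0.5 = 7.51. Power at 34 is 0.757 and the minimum is 38.
- f = 0.235, ρ = 0.555: power is 0.778 at 32 and 0.804 at 34, so the minimum is again 34.

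So 34 arises from f of about 0.235 to 0.25 with ρ of about 0.5 to 0.555.

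**Step 2: what that f means.** Let the arms start equal and differ by δ at post-test. The four cell means are 0, 0, 0, δ. The grand mean is δ/4, and the arm and occasion means are 0 and δ/2. The interaction residual in the last cell is δ − δ/2 − δ/2 + δ/4 = δ/4, and it is ±δ/4 in every cell. Hence f = δ/(4·SD).
- f = 0.25 means δ = 4 × 0.25 = 1.00 SD.
- f = 0.235 means δ = 4 × 0.235 = 0.94 SD.
- δ = 0.47 SD means f = 0.47/4 = 0.1175.

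This step does not involve ρ. Either route to 34 assumes about twice the cited effect.

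**Step 3: power for 0.47 SD at ρ = 0.5.**
- N = 34: λ = 0.01380625 × 34 × 2/0.5 = 1.88, power 26.5%.
- N = 40: λ = 0.01380625 × 40 × 2/0.5 = 2.21, power 30.5%.
- N for 80% power: 146 (λ = 8.06, power 0.805).
- Detectable difference at 80% power: 0.99 SD with 34, 0.91 SD with 40.

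**Step 4: vary ρ for 0.47 SD.**

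| ρ | Power, N = 34 | Power, N = 40 | N for 80% |
|---|---|---|---|
| 0 | 16% | 18% | 288 |
| 0.3 | 20% | 23% | 202 |
| 0.5 | 26.5% | 30.5% | 146 |
| 0.7 | 40% | 46% | 88 |
| 0.8 | 56% | 63% | 60 |

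Power reaches 80% at ρ of about 0.87 with 40 mothers and about 0.89 with 34.

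**Cross-check.** A two-sample t test on change has standardised effect δ/(SD·√(2(1 − ρ))), so its squared noncentrality is (N/4)·δ²/(2(1 − ρ)·SD²) = N·δ²/(8(1 − ρ)·SD²). Substituting f = δ/(4·SD) in λ gives the same expression, so the powers agree.

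**The case against.** The best defence is that ρ is not reported and a high value would rescue the claim: a correctly converted 0.47 SD does reach 80% with 34 mothers at ρ of about 0.89. That is arithmetically true. But the article claims no such correlation, and it does not fit the article's own number: at ρ = 0.8 already, f = 0.25 would have returned 16 and f = 0.235 would have returned 18, not 34. Nor does it help to read d = 0.47 in units of the SD of change. Power is then 26.5% with 34 and 30.5% with 40 whatever ρ is.

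Other parts of the defence stand and limit what can be said.
- A reader might infer that true power is simply about 30%. The documents do not support that as a fact; it depends on ρ = 0.5. Power with 40 passes one half at ρ of about 0.73, so even a non-significant result being more likely than not is conditional.
- A reader might infer a second, separate error, because d/2 gives 38 at the default correlation. That is not established, since d/2 gives 34 at ρ of about 0.555. What was entered is inferred, not documented.
- A reader might infer that a null result would be misread as lack of efficacy. The article does not say how a null result would be interpreted.
- The analysed number is uncertain. Recruitment plans 20% oversampling: 34 × 1.2 = 40.8 suggests that 40 already includes it, while 40 × 1.2 = 48 is the other reading. At ρ = 0.5, power is 26.5%, 30.5% and 36% for 34, 40 and 48 analysed mothers. None is near 80%.
- A baseline-adjusted analysis would have more power, but Statistical analyses plans condition-by-time models and mentions no such adjustment, so its power cannot stand in for that of the planned analysis.

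**Conclusion.** Wrong as written. The stated minimum of 34 corresponds to a difference in change of 0.94 to 1.00 SD, about twice the 0.47 it is said to be based on, and this holds on either route that reproduces 34. For 0.47 SD, power with all 40 mothers analysed is 18% to 63% over ρ from 0 to 0.8.

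That power is well below 80% is robust for any ρ up to 0.8. The particular values 26.5%, 30.5% and 146 rest on ρ = 0.5, complete data at the stated N, and d measured in units of the outcome SD at one occasion. The claim of more than 80% power for the third and fifth aims has no support from this calculation, because it takes main-effect power as its reference point.

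**What to change.** Keep the planned 40 mothers. In Sample size and power:

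1. Delete the sentence giving 34 as the minimum, and state the f and the pre-post correlation that were entered.
2. Put in its place, for example: With 20 mothers per arm analysed and an assumed pre-post correlation of 0.5, the condition-by-time test has power of about 30.5% for a between-arm difference in change of 0.47 SD (18% to 63% for correlations from 0 to 0.8). The difference detectable with 80% power is about 0.91 SD (0.99 SD if 34 are analysed).
3. Withdraw the claim of more than 80% power for the third and fifth aims so far as it rests on this calculation.
4. State that intervention effects will be reported as estimates with 95% confidence intervals.

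The cost is wording only. Design, sample and planned analysis are unchanged; the stated power becomes less favourable.

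### The power of more than 80% claimed for the third and fifth aims is not derived and not ensured by the design, and the fifth aim is not a mediation question

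*Protocol article*

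**What the plan says.** Sample size and power (Protocol article) sizes the primary, secondary and fourth aims through "repeated measures ANOVA within-between interaction, G*Power 3.1.9.2". The significance level is 0.05 and the target power 80%, and the outcome of the calculation is given as "a medium-sized effect of *d* = 0.47, a minimum sample size of *n* = 34 is required". For the third and fifth aims, both described there as tests of mediation, it gives no calculation and states that "the proposed sample size ensures a power >80% since the power to detect mediating effects is generally larger than it is for main effects".

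Aims and hypotheses describes the fifth aim differently: to "compare the SUD experimental group and the SUD control group to the low-risk group with respect to post-test measures". The Fifth aim paragraph under Measures repeats that description. Statistical analyses nevertheless assigns the third and fifth aims together to the Montoya and Hayes repeated-measures mediation approach.

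On numbers, Recruitment says "The SUD group (*n* = 40) will be composed of women with a history of SUD diagnosis" and "The low-risk group (*n*=20) includes mothers recruited from the general population". Randomization specifies the SUD sequence "with a 1:1 allocation using random block sizes of 2 and 4", so 20 mothers per arm.

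**The concern.** The claim is a guarantee, and it rests on one general statement about mediation tests.

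- **Fifth aim.** It contrasts groups and has no mediator, so a statement about mediation power says nothing about it.
- **Third aim.** An indirect effect is the product of the arm-to-mediator path and the mediator-to-parenting path. The first path is what the secondary aim tests, in the same mothers and at the same d = 0.47. Requiring a second path to be detected as well cannot make success more likely than detecting the first alone, if both must be significant.

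Whether the cognitive processes carry the effect is one of the study's main empirical rationales in the Abstract and Discussion. If the report repeats a power above 80%, a null indirect effect could be read as evidence against the mechanism when the trial may have had little chance of detecting it.

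**Working it through.** **Inputs from the protocol:** d = 0.47; α = 0.05; target power 0.80; minimum n = 34; 40 SUD mothers at 1:1 (20 per arm); 20 low-risk mothers.

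**Assumptions, because the protocol gives no value:** pre-post correlation ρ = 0.5; standardised mediator-outcome slope b from 0.3 to 0.7; two-sided tests; 40 taken to include the 20% oversampling (34 × 1.2 = 40.8).

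**Step 1: the protocol's own n = 34.** For the within-between interaction with two groups and m = 2 occasions, the noncentrality is λ = f²·N·m/(1 − ρ).
- f = 0.25 (conventional medium effect): λ = 0.0625 × 34 × 2/0.5 = 8.5, power 0.807. This reproduces n = 34.
- f = d/2 = 0.235: power 0.757 at 34, 0.805 at 38 and 0.826 at 40, so the minimum is 38.

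The noncentrality for a t test on change scores is δ²N/4, with δ in SD units and SD of change equal to 1 when ρ = 0.5. Setting this equal to 4f²N gives δ = 4f. So f = 0.235 means a difference in change of 0.94 SD, and f = 0.25 means 1.0 SD. A plain difference of 0.47 SD is f = 0.1175.

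**Step 2: arm-to-mediator path alone (N = 40).**
- Plain 0.47 SD: power 0.305.
- 0.94 SD (f = 0.235): power 0.826.

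**Step 3: third aim by joint significance.** Simulated trials with M = δ·arm + error and Y = b·M + error, residual variance 1 − b² and no direct effect. Success requires arm-to-M, and M-to-Y given arm, each to be significant at 0.05. Figures are simulation estimates.

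| Reading of 0.47 | N | b = 0.3 | b = 0.5 | b = 0.59 | b = 0.7 |
|---|---|---|---|---|---|
| Plain 0.47 SD | 40 | 0.14 | 0.27 | 0.30 | 0.30 |
| Plain 0.47 SD | 34 | 0.10 | 0.22 | 0.25 | 0.26 |
| f = d/2 (0.94 SD) | 40 | 0.38 | 0.75 | 0.81 | 0.825 |
| f = d/2 (0.94 SD) | 34 | 0.30 | 0.65 | 0.73 | 0.756 |

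On the more generous f = 0.25, which is what reproduces n = 34, power runs from 0.40 (b = 0.3) through 0.78 (b = 0.5) to 0.87 (b = 0.7) at N = 40. At n = 34 it runs from 0.31 to 0.80.

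**Step 4: fifth aim.** Two-sample t test, noncentrality d/√(1/n₁ + 1/n₂).
- Difference detectable with 80% power: d = 0.91 for 20 versus 20; d = 0.78 for 40 versus 20.
- If the true gap happened to be 0.47: 0.47/√(1/20 + 1/20) = 1.49, power 0.30; 0.47/√(1/40 + 1/20) = 1.72, power 0.39.

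**Step 5: descriptions of the fifth aim, side by side.** Aims and hypotheses and the Fifth aim paragraph describe a comparison of groups. Sample size and power and Statistical analyses treat it as mediation. The two cannot both stand.

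**The case against.** **Mediation tests can out-power tests of the total effect.** This is true when both paths are large. If a total effect of d = 0.47 were fully mediated through two equal standardised paths of 0.478 (arm-to-mediator d about 1.09), joint-significance power at N = 40 would be 0.73 against 0.30 for the total effect. But the protocol assumes no such paths, and this favourable case still falls short of 0.80.

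**The ceiling belongs to one test.** This stands. The protocol names the Montoya and Hayes approach, not joint significance. On the plain reading at b = 0.7, percentile-bootstrap power was 0.35 to 0.38 against 0.30 by joint significance. The ceiling is a good approximation, not a proof for every test.

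**A tempting stronger reading.** A reader might infer that the protocol's own d = 0.47 fixes power at roughly 13 to 40% for both aims, so that the claim is numerically disproved. The documents do not support that, for three reasons.
- They give no mediator-outcome slope; the low end comes from choosing 0.3.
- They enter 0.47 through G*Power's interaction test, where it stands for a much larger difference in change. On that convention some slopes do give more than 80%.
- They offer 0.47 as the intervention effect, never as the gap between SUD and low-risk mothers. The 0.30 and 0.39 for the fifth aim are therefore illustrations, and a true gap of 0.78 to 0.91 SD would reach 80%. Pooling the two SUD arms is not stated either.

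**These are lower-ranked aims.** Also true: neither the sample size nor the primary analysis depends on the sentence.

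**Conclusion.** The concern holds in this form: power above 80% for the third and fifth aims is asserted without derivation, and the design does not ensure it.

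For the fifth aim this needs no assumption, since the reason given concerns mediation and the aim contains none. For the third aim, power at N = 40 is about 0.14 to 0.30 or about 0.38 to 0.82, depending on how 0.47 is read. Both ranges rest on assumed slopes of 0.3 to 0.7 and a joint-significance test, and the second also on ρ = 0.5. On the f = d/2 convention, 0.80 is passed only with a strong mediator-outcome link (slope about 0.59 or more), and with 34 mothers it is not reached. Rounding up to f = 0.25 does not rescue the guarantee: a slope of 0.5 still gives 0.78 at N = 40. Loss of mothers beyond the oversampling allowance would lower all these figures.

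What is shown is an unsupported guarantee. No single true power value is established.

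**What to change.** 1. Delete the sentence claiming more than 80% power for the third and fifth aims.
2. Third aim: either state the assumed arm-to-mediator and mediator-outcome paths with the resulting range of power, or label the aim exploratory and report indirect effects with confidence intervals. Do not replace the claim with one narrow figure such as 0.13 to 0.38, which would depend on slopes and a reading of d that the protocol does not state.
3. Fifth aim: give the difference detectable with 80% power, about d = 0.91 for one SUD arm of 20 against 20 low-risk mothers. Quote about 0.78 only if the two arms are to be pooled (40 versus 20), and say so.
4. Correct Sample size and power and Statistical analyses so that the fifth aim is described and analysed as a group comparison.

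The cost is wording and one reassigned analysis method. Sample size, randomisation and the primary analysis are unchanged. The drawback is that the stated power becomes less favourable.
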